#### Process evaluation

To collect qualitative feedback on programme implementation, focus groups will be conducted after the intervention delivery with a sub-sample of adolescents, caregivers and intervention delivery staff from the intervention group. The focus groups will have around 6–8 participants with at least four focus groups conducted in each country (with caregivers, adolescents, facilitators and supervisors). In addition, approximately 20 family members from the intervention group families (eg, grandparents) who were not part of the dyad enrolled in the trial will be interviewed in each country to explore intervention experiences, acceptability and perceived impacts in the wider family. Furthermore, 10–15 interviews with professionals will be conducted per country to further progress understanding of the delivery context and potential scale-up (Shenderovich *et al*, forthcoming). A survey of the ALTERNATIVA and HYA networks will also be conducted to look at programme dissemination.

### Statistical analyses

Prior to effectiveness analyses, descriptive statistics, internal consistencies and correlations will be examined for all study variables. Descriptive statistics will be reported separately for each country and for the total sample. Drop-out analyses will be conducted to compare completers and non-completers of the assessments using analysis of variance and χ² tests. Primary analyses will compare intervention and waitlist control groups at post-intervention and 6-month follow-up using an intention-to-treat approach. No interim analyses are planned. Missing data will be handled via multiple imputation or full information maximum likelihood.

Treatment effects over time will be estimated using baseline-adjusted linear mixed models including fixed effects for treatment group, time and the treatment-by-time interaction, with random intercepts to account for families nested in groups and repeated observations. The treatment effect will be estimated using baseline-adjusted linear mixed models including treatment, time and treatment-by-time interaction terms. To this end, we will use linear mixed models with random intercepts, accounting for clustering at the group or site level, as appropriate, using robust standard errors or multilevel modelling approaches. Effect estimates, CIs and exact p values will be reported for the prespecified outcomes. Analyses will be performed in Mplus, Stata or R, using robust methods or multilevel models.

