### Study setting

Intervention implementation is conducted in two Eastern European countries, North Macedonia and Moldova, and is supported by two established health networks with prior experience delivering PLH programmes. In North Macedonia, the Institute for Marriage, Family and Systemic Practice (ALTERNATIVA) comprises a network of psychologists, social workers and family therapists engaged in research and education on systemic practice and family psychotherapy. In Moldova, the Health for Youth Association (HYA) supports publicly funded youth clinics that deliver preventive and therapeutic services addressing sexual and reproductive health, psychological well-being, substance misuse and violence prevention.

The intervention is scheduled to be delivered to the intervention group between fall 2025 and summer 2026. In Moldova, implementation will occur in a single wave, while in North Macedonia it will be conducted in two waves, based on the feasibility of recruiting families. This approach is consistent with procedures successfully used in North Macedonia during phase 2 of the FLOURISH project.

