### Sample size

We performed a simulation-based power analysis for a baseline-adjusted linear mixed model with random intercepts for families nested in clusters, a fixed effect for treatment (PLH vs waitlist), timepoint (postintervention, follow-up), the treatment-by-time interaction and baseline measures as a covariate, using the R- package simr.^35^ We assumed an effect size of Cohen’s d=0.25 for the treatment effect at post-intervention, a within-person correlation of r=0.6 between baseline, post-intervention and follow-up measures, a between Intracluster Correlation Coefficient of 0.01, an alpha level of 0.05, and no further gains or losses at follow-up compared with post-intervention. Simulation results (1000 iterations) indicated that 62 clusters, each consisting of 10 families, achieve 84% power to detect an effect size of Cohen’s d=0.25 at postintervention and 82% power for the likelihood ratio test, comparing the model that includes the baseline covariate, time, the treatment main effect and the treatment-by-time interaction to the reduced model that contains only the baseline covariate and time. To achieve this sample size requirement in the presence of dropout, we plan to recruit 64 clusters and allow for cluster sizes slightly exceeding 10 families.

While the anticipated individual-level effects may be modest, as this is a preventive intervention, even small effects can translate into meaningful public health benefits when applied across a large number of individuals. Small shifts in risk or symptom trajectories, when sustained and broadly implemented, have the potential to prevent a substantial number of adverse outcomes and reduce downstream clinical burden.

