### Randomisation and blinding

This study will involve a multicountry, cluster/group randomised controlled trial of the adapted PLH programme. Clusters will be randomly assigned to either the intervention group or the waitlist control group (see online supplemental appendix 3 figure S1 for the study flow chart). Each group (intervention and waitlist control) will consist of 10 adolescent–caregiver pairs, with a total of 32 groups per country, implemented across 16 sites in North Macedonia and 16 sites in Moldova.

Randomisation will occur at the group level and be based on predefined clusters with two clusters embedded within each geographical region (ie, school or youth clinic A and B). Stratified randomisation with country as the strata will be employed. A total of two sets with 16 sites/clusters will be randomised within each of the countries for a total of 64 sites/clusters overall. In North Macedonia, eligible site/clusters will be primary schools in Macedonian-speaking and Albanian-speaking urban and suburban areas of the Skopje metropolitan region. In Moldova, site/clusters will be Youth Clinics or schools. Across both countries, two clusters (ie, groups) per geographical region will be randomly assigned to either the intervention or the waitlist control condition.

The list of sites/clustered will be provided to the University of Klagenfurt, randomisation will be conducted independently by the University of Klagenfurt and provided to the research coordinators in North Macedonia and Moldova. The random allocation sequence will be generated by the project coordinator at the University of Klagenfurt using a computerised randomisation tool. Participants and data assessors will be blinded during informed consent and baseline assessments. After baseline is completed, participants will be informed of their allocation to intervention group or waitlist. Data assessors will remain blinded during the post and follow-up assessments. Pre, post and follow-up data sent to the analysis team will remain blinded until analyses are completed and shared with the team. To minimise assessment bias, different researchers will be responsible for outcome assessments and process monitoring.

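### The stated primary model has no country term although randomisation is stratified by country, and the clustering level is left open; if a country gap survives baseline adjustment, the reported standard error can be too large and power is lost

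*Protocol article*

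**What the plan says.** Under Randomisation and blinding, the protocol article states: "Stratified randomisation with country as the strata will be employed". The same section places two clusters in each region and says that "two clusters (ie, groups) per geographical region will be randomly assigned to either the intervention or the waitlist control condition". It counts 32 groups per country at 16 sites per country, so a site there holds two groups. It then refers to 64 sites or clusters overall, so a site there is a single group.

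Under Statistical analyses, the treatment effect comes from a baseline-adjusted linear mixed model with "fixed effects for treatment group, time and the treatment-by-time interaction, with random intercepts to account for families nested in groups" and repeated observations. The next sentence restates the same fixed terms. Clustering may be handled at either group or site level, by robust standard errors or multilevel modelling. The model simulated under Sample size has the same terms: baseline, treatment, time, treatment-by-time, and random intercepts for families within clusters.

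None of these three statements contains country. Country appears only in the descriptive statistics and, under Additional exploratory analyses, in multigroup comparisons.

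**The concern.** A factor used to stratify randomisation normally belongs in the analysis model. Stratifying balances the countries across arms, so a difference in country means cancels out of the treatment contrast and adds nothing to its true sampling error. If the model has no country term, the same difference goes into the random intercept for group and is treated as unexplained variation between clusters. The reported standard error is then larger than the true one, the confidence interval is too wide and the test is conservative.

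A residual gap is plausible. The countries differ in delivery network, language and recruitment channel. They also differ in setting (schools in one, Youth Clinics or schools in the other) and in timing: "In Moldova, implementation will occur in a single wave, while in North Macedonia it will be conducted in two waves". The margin is thin, because planned power is only 84% at post-intervention and 82% for the likelihood ratio test.

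**Working it through.** **Inputs from the Sample size section.**
- Clusters: K = 62, with m = 10 families each; stated power 84%.
- Effect: "We assumed an effect size of Cohen’s d=0.25 for the treatment effect at post-intervention".
- Correlation among one person's repeated scores: r = 0.6.
- ICC for clusters: 0.01.
- Alpha: 0.05 (two-sided assumed, as the sidedness is not stated).

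**Assumed input.** δ is the country difference left after baseline adjustment, in residual SD. The documents give no value, so 0 to 0.5 is shown. Arms are taken as balanced within country.

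**Step 1: reproduce the plan's figure.** With residual variance 1,

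SE = √[(4/K)(ICC + (1 − ICC)/m)] = √[(4/62)(0.01 + 0.099)] = 0.0839.

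Power = Φ(0.25/0.0839 − 1.96) = 84.6%, or 83.5% with a t reference on 60 df. The stated 84% is reproduced. This requires d = 0.25 to be expressed in the SD that remains after baseline adjustment. With residual variance 1 − 0.6² = 0.64, power would be 96.1%.

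**Step 2: omit country and cluster on group.** A gap δ between two equal halves adds δ²/4 to the variance of the cluster means:

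reported SE = √[(4/K)(0.109 + (δ²/4)·K/(K − 2))].

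The true SE stays at 0.0839, so true power = Φ((0.25 − 1.96 × reported SE)/0.0839) and true type I error = 2Φ(−1.96 × reported SE/0.0839).

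Example, δ = 0.3: 0.0225 × 62/60 = 0.02325; reported SE = √[(4/62)(0.13225)] = 0.0924.

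| δ (residual SD) | Reported SE | Excess | Type I error | Power |
|---|---|---|---|---|
| 0 | 0.0839 | 0% | 5.0% | 84.6% |
| 0.1 | 0.0848 | 1.2% | 4.7% | 84.1% |
| 0.2 | 0.0877 | 4.6% | 4.0% | 82.4% |
| 0.3 | 0.0924 | 10.2% | 3.1% | 79.5% |
| 0.5 | 0.1058 | 26.2% | 1.3% | 69.4% |

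With country in the model, the SE is 0.0839 and power 84.6% in every row. With the 64 clusters to be recruited and no loss, power without country is 85.7% at δ = 0, 80.8% at 0.3 and 71.1% at 0.5.

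**Step 3: check by simulation** (64 clusters paired within region, 3000 runs).
- δ = 0.3: mean reported SE 0.0904 without country and 0.0821 with it; power 78.9% and 84.4%.
- δ = 0.5: SE 0.1036 and 0.0822; power 70.3% and 84.3%.
- The empirical SE of the estimate was about 0.083 to 0.084 in both cases, so only the reported SE is wrong.
- A baseline gap of 0.5 SD carried entirely by the baseline covariate caused no inflation (0.0821 against 0.0820).

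**Step 4: what size of gap is plausible.** If a country gap D (in raw SD) is stable over time and the baseline slope is 0.6, adjustment leaves 0.4D. Divided by the residual SD √0.64 = 0.8, that is 0.5D. Residual gaps of 0.1, 0.3 and 0.5 then correspond to stable raw gaps of 0.2, 0.6 and 1.0 SD.

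**Step 5: the region pair.** If the whole ICC of 0.01 were variance between regions or countries, the excess would be √(0.109/0.099) = 1.049, about 5%, and power with the term included would be 87.9%. In simulation with region variance 0.01, the SE was 0.0826 without a pair term and 0.0781 with one; power was 85.2% and 86.5%.

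**The case against.** **The detail may be in the analysis plan.** The article says that a statistical analysis plan will be made public, it is not shown here, and the model is described as including the listed terms, not as limited to them. Country may therefore be added there. This has some force. But the article does list its fixed effects, and gives the complete model used for power; that list does not match the stated design. Adding country after unblinding would look post hoc.

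**The region pair may already be covered.** Clustering at site level is one of the two options the text allows. If a site is the pair and each pair has one group per arm, any country shift cancels within the pair. In a check with 32 pairs and no country term (4000 runs), the site-level robust SE stayed at 0.0817 to 0.0818 for gaps from 0 to 0.63 residual SD, while the group-level SE rose from 0.082 to 0.115. This stands: the inflation arises under only one of the two options. A reader might infer that the plan ignores region altogether. The text does not support that. It supports only that the level is left open and that site has two meanings.

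**The harm is conditional.** A reader might infer that between-country variance is known to inflate the standard error. The documents give no residual country gap, and at 0.1 to 0.2 residual SD the loss is small. Nor do they say whether the ICC of 0.01 already contains country variance; if it does, the inflation is at most about 5%. Inflation well above 20%, or power near 60%, needs large assumed gaps.

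**Conclusion.** The point holds as a mismatch between the declared stratum and the stated model, with a conditional, one-sided consequence. If the model clusters on group without country, and 0.1 to 0.5 residual SD of country difference survives baseline adjustment, the reported SE is about 1% to 26% too large, type I error falls to between 4.7% and 1.3%, and power falls to between about 84% and 69%. Power drops below 80% at about 0.3 SD, which on the protocol's r = 0.6 means a stable raw gap of about 0.6 SD.

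These figures assume arms balanced within country, country variance on top of the stated ICC, and d scaled to the residual SD. If residual variance were 0.64 instead, power would start at 96% and still be 84% at a gap of 0.5 raw SD.

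A reader might infer that leaving country out biases the treatment effect or raises the risk of a false positive. It does neither: with balanced arms the estimate and its true precision are unchanged and type I error stays below 5%. The cost is over-wide intervals and lost power. The region part is a smaller matter of clarity, worth about 5% on the SE at the protocol's own ICC.

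**What to change.** - Add country and country-by-time as fixed effects in the primary and secondary models, and put the same terms in the power simulation.
- Define site once, as either the pair or the single group.
- Replace the open choice of clustering level with a fixed rule: a random intercept for the region pair above the group intercept or, if robust standard errors are used, the pair as the clustering level.
- A term for delivery wave in North Macedonia is optional.
- State whether d = 0.25 refers to the raw or the residual SD, and whether the ICC of 0.01 includes variance between countries or regions.

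The cost is a short change of wording and one or two degrees of freedom out of about 60 clusters, with no new data. If there is no country gap, the country term costs practically nothing: simulated power was 85.4% with it and 85.5% without. Entering the pairs as fixed effects would cost slightly more when regions do not differ (84.2% against 85.5%), which is a reason to prefer the random intercept.

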#### Health economic evaluation

We will conduct a within-trial economic evaluation, which will include a cost–utility analysis with cost per QALY and a cost-effectiveness analysis using cost per CWLY as respective outcome measures. The economic evaluation will be conducted from a health and social care sector perspective and will explore spill-over effects towards informal care, adolescent’s educational attainment and caregiver’s productivity losses. Costs of direct intervention delivery and costs due to caregiver self-reported and proxy-reported health and social care resource use will be considered. Our economic evaluation will yield incremental cost-effectiveness ratios and net benefit estimates comparing the intervention group to the wait-list group. Uncertainty will be assessed using bootstrapping and sensitivity analyses.

#### Quantitative implementation analyses

Quantitative process evaluation measures of programme implementation will be analysed using descriptive statistics, correlation and regression analyses. Associations of group session and catch-up session attendance with demographic characteristics of participants (eg, age, gender) will be checked for potential inequalities of access. Associations between facilitator experience and fidelity of delivery will be explored through correlation analyses.

Within the intervention group, associations will be explored between implementation indicators (eg, attendance and fidelity) and intervention outcomes. Indirect effect models will test the theories of change and implementation measures as mediators of outcome. Complier average causal effect models may also be employed to assess associations between intervention attendance and outcomes, depending on attendance distribution.

#### Qualitative analyses

The qualitative data collected from focus groups and interviews will be analysed using thematic analysis.

#### Scalability and financing strategies

We will gather stakeholder input, for example, through professional expert advisory groups, to assess the fiscal space and policy options for sustainable financing. We will conduct a macroeconomic analysis, including a public financing landscape summary, identifying funding mechanisms as well as a budget impact analysis based on coverage scenarios. We will produce a potential investment case for the intervention, including fiscal justification and prioritisation within the national budget. We plan to explore opportunities for scale-up and potential integration points within existing fiscal mechanisms in primary care, public education and local governments’ budget envelopes.

Furthermore, drawing on findings related to effectiveness, cost, cost-effectiveness and stakeholder views on scalability, simulation modelling will be used to examine potential scenarios for scaling the adapted PLH programme in Moldova and North Macedonia. We will conduct agent-based modelling, a simulation approach that models the outcomes of policy implementation based on three core components: agents, rules and environments.^42^ This method enables the investigation of complex, system-wide and long-term policy effects that are not feasible to evaluate through experimental designs. A scale-up strategy will be developed guided by this information.

#### Additional exploratory analyses

Additional exploratory analyses will compare the intervention and waitlist control groups on other prespecified outcomes at baseline, postintervention and 6-month follow-up. Multigroup analyses will be conducted to compare models across countries and demographic subgroups (eg, adolescent and caregiver gender). This analysis may inform and feed into the scale-up strategy in terms of potential coverage and outreach in the general population and inform the budget impact analysis of the intervention.

### Patient and public involvement

Advisory groups consultations with adolescents, caregivers, HYA and ALTERNATIVA staff and external professionals have been conducted in each phase of the FLOURISH project to obtain feedback on the results and to inform implementation and recruitment strategies, including for the randomised trial described here. Advisory group consultations will continue during the trial to inform programme scale-up considerations.

## Ethics and dissemination

The FLOURISH project has received ethical approval from (1) the Institutional Review Board for Research Ethics at the University of Klagenfurt in Austria (approval number: 2023-013), (2) the National Committee of Ethical Expertise for Clinical Trials of the Ministry of Health of the Republic of Moldova (approval number: 1476) and (3) the Ethical Commission for Human Research at the Medical Faculty, St. Cyril and Methodius University, Skopje, North Macedonia (approval number: 03-2144/4). Consistent with the Horizon Europe guidelines for clinical trials, modifications to the project are submitted in ethical amendments to the ethics boards.

The project adheres to established guidelines and recommendations to ensure clinical safety and efficacy. Oversight of ethics-related matters is provided by an independent Data Safety and Management Board (DSMB) and an Ethical Advisor (EA), who ensure compliance with key ethical standards, including the Declaration of Helsinki (2013). A Memorandum of Understanding between the project coordinator, the DSMB and the EA outlines the roles and responsibilities of each party. To safeguard both staff and participants, a Data Collection Safety Protocol and an AE Reporting Form were developed. All personnel involved in research activities and intervention delivery received training to identify and report AEs and serious AEs (SAEs), in accordance with the protocol and using the standardised AE form designed for the FLOURISH project. AE monitoring helps to detect any potential risks associated with assessments or intervention procedures. In the event of a SAE, a thorough investigation was carried out, and detailed reports were submitted to the relevant ethics committees and the DSMB to determine whether study procedures required modification. If it is decided that the SAE is related to the study, the DSMB and ethical boards may recommend changes. The DSMB and ethical boards will determine whether to proceed with the study, proceed with minor or major changes, or stop the study until concerns have been addressed. The feasibility and effectiveness of these safety procedures were assessed and updated during phase 1 to ensure robust monitoring throughout the project.

All data collected in FLOURISH will be handled with confidentiality and in compliance with the General Data Protection Regulation. A comprehensive data management plan was developed, outlining detailed procedures for data collection, access, deletion and secure storage. Prior to enrolment, participants are fully informed about the types of data to be collected. Data collected on paper will be stored in locked cabinets at the respective institutions responsible for data collection. Personal data (for participant contact and session monitoring during the intervention) and video recordings of the PLH sessions (for facilitator supervision and quality assessment) will not be shared across sites. This data will be securely stored locally in North Macedonia (ALTERNATIVA) and Moldova (HYA). Only select members of the local FLOURISH team will have access to this data. Anonymised data will be managed by the University of Klagenfurt, who is responsible for overall data management. Only anonymised datasets will be shared among project partners. To ensure data security, all project data will be backed up on two additional password-protected servers and/or external hard drives managed by the IT department at the University of Klagenfurt.

All project members have received training and certification in human subject research and ethical data management in accordance with relevant guidelines. The study protocol and statistical analysis plan will be made publicly available through the Zenodo repository and can also be obtained on reasonable request from the corresponding author. Anonymised quantitative data will be preserved and curated in Zenodo to ensure long-term accessibility.

The FLOURISH project uses a comprehensive communication and dissemination strategy tailored for families, implementers and other policy stakeholders. Dissemination efforts focus primarily on stakeholders in North Macedonia and Moldova to foster discussions on family policies, adolescent health and the scalability of parenting programmes, while also seeking to engage actors across the wider Eastern European region.

This multicountry hybrid type 1 effectiveness-implementation randomised waitlist-controlled trial aims to assess the implementation and (cost-)effectiveness of the adapted PLH programme in the Republic of North Macedonia and the Republic of Moldova. The study uses a waitlist control group as the comparator, allowing all participants to receive the adapted PLH programme while maintaining a rigorous evaluation of its effectiveness. Additionally, a scaling-up strategy will be developed, guided by a variety of data sources. This approach aims to advance the adoption and expansion of open-source, evidence-informed family interventions for adolescents and caregivers in low-resource settings, with the goal of reducing risks for mental health problems among families in Eastern Europe.
